### Explicit Condition

Within the explicit condition, gait training is organized by creating a learning environment that is (more) explicit in nature. Practice will be organized based on the characteristics of explicit motor learning as reported under the explicit condition in Figure 1. The condition is similar to the first (cognitive) stage of motor learning according to Fitts and Posner [34] that is characterized by the use of many explicit instructions, explaining precisely how motor skills should be performed. This stage is verbal and cognitive of nature. Contrary to the implicit condition, the explicit condition strives to maximize the number of explicit verbal instructions. The explicit instructions that have been used in the trial will be documented by the therapist’s in treatment logs.

### Measurements

All measures will be assessed by independent, blinded, and trained assessors at 3 assessment points (T0, T1, and T2; Table 1) and will take place at the participant’s home. The primary outcome parameter is walking speed measured in meters per second using 10MWT. First, demographics are described, and then, the primary and secondary outcome measures are reported.

### Demographics

At baseline, the following demographic and prognostic information is collected (T0): age, gender, time post stroke, affected side, walking aids, educational level, cognitive level (Montreal Cognitive Assessment, MoCA) [35], static balance and fall risk (Berg Balance Scale) [36], measures of mobility and disability (Rivermead Mobility Index) [37], and ability to make movements outside the synergetic patterns (Fugl-Meyer assessment of the lower limb) [38]. To assess the propensity for conscious motor processing, the Dutch version of Movement Specific Reinvestment Scale (MSRS) is used [39,40].

### Walking Performance Measures

Walking performance is measured using the 10MWT [41] and the Dynamic Gait Index (DGI) [42]. To assess the robustness of the obtained performance, walking will also be assessed over a longer period (1-month follow-up) and under secondary task loading.

#### 10-Meter Walking Test

Gain in walking speed has been associated with a transition to a higher class of ambulation, resulting in a better function and quality of life [41,43]. Next to statistical significance, the MCID will be used to assess clinical relevant differences. The MCID for walking speed in people after stroke has been established at the minimal difference of 0.16 m/s [33]. Exceeding this threshold indicates that the participants obtained a clinically meaningful improvement.

**Table 1 table1:** Overview of measurements used in this study.

Data		Time	ICF^a^ level
**Demographics**			
	Age, gender, time post stroke, affected or nonaffected side, walking aids, educational level	T0	Personal factors
	Montreal Cognitive Assessment	T0	Body functions and structure
	Berg Balance Scale	T0	Activity level
	Rivermead Mobility Index	T0	Activity level
	Fugl-Meyer Assessment	T0	Body functions and structure
**Walking performance**			
	10-meter walking test	T0, T1, T2	Activity level
	Dynamic Gait Index	T0, T1, T2	Activity level
	Dual task	T0, T1, T2	Activity level
**General outcome measures**			
	Movement Specific Reinvestment Scale	T0, T1, T2	Personal factors
	Verbal protocol	T2	N/A^b^
	Stroke Specific Quality of Life Scale	T0, T2	Participation level
	Global Perceived Effect scale	T2	N/A

^a^ICF: International Classification of Functioning, Disability, and Health.

^b^N/A: not applicable. The ICF level is not applicable for the Verbal Protocol and Global Perceived Effect Scale as these measures do not examine health or disability but evaluate the intervention.

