**Methods:**

The study adopts a randomized, controlled, single-blinded study design. People after stroke will be eligible for participation when they are in the chronic stage of recovery (>6 months after stroke), would like to improve walking performance, have a slow walking speed (<1 m/s), can communicate in Dutch, and complete a 3-stage command. People will be excluded if they cannot walk a minimum of 10 m or have other additional impairments that (severely) influence gait. Participants will receive 9 gait-training sessions over a 3-week period and will be randomly allocated to an implicit or explicit group. Therapists are aware of the intervention they provide, and the assessors are blind to the intervention participants receive. Outcome will be assessed at baseline (T0), directly after the intervention (T1), and after 1 month (T2). The primary outcome parameter is walking velocity. Walking performance will be assessed with the 10-meter walking test, Dynamic Gait Index, and while performing a secondary task (dual task). Self-reported measures are the Movement Specific Reinvestment Scale, verbal protocol, Stroke and Aphasia Quality of Life Scale, and the Global Perceived Effect scale. A process evaluation will take place to identify how the therapy was perceived and identify factors that may have influenced the effectiveness of the intervention. Repeated measures analyses will be conducted to determine significant and clinical relevant differences between groups and over time.

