#### Stroke and Aphasia Quality of Life Scale

The *Stroke and Aphasia Quality of Life Scale (* SAQOL-39) is assessed at baseline and after the intervention to measure the health-related quality of life [53]. The questionnaire contains 39 items and is developed for people after stroke and is feasible to use for people with aphasia. The SAQOL-39 is a short version of the original SAQOL (53 items) and has shown to be an acceptable, reliable, and valid measure of the health-related quality of life [53].

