### Data Analyses

Baseline scores of demographic and prognostic data and primary and secondary outcome measures will be used to compare the 2 groups. Only data of the participants who attended minimum of 7 or more of the therapy sessions will be considered as adherent and processed in the statistical analysis. Statistical analysis will be conducted to determine significant differences between groups and over time (baseline and postintervention performance). A repeated measure analyses will be used to compare the 2 groups (implicit and explicit) at 3 different time points (before, after, and after 1-month follow-up). Post hoc tests with correction for multiple testing will be used to explore effects over time and between groups. Subgroup analysis will be performed on cognition (MoCA score <21) [35]. An alpha level of .05 will be set for all tests. The primary outcome measure, walking speed, will also be described with reference to clinically relevant differences between groups (MCID: 0.16 m/s) [33]. All datasets used or analyzed during this study are available from the corresponding author on a reasonable request.

Data will be analyzed according to an intention-to-treat and per-protocol principle. In the intention-to-treat, data of the participants are analyzed according to their original treatment allocation. If self-reported (subjective) and audio-recorded (objective) data reveal that cases are not delivered as intended, then the analyses will be performed using the per-protocol principle. Within this study, protocol deviations are defined as “deviations from the protocol that occur in two or more sessions.” If protocol deviations were observed, then data from this person were not included in the per-protocol analysis. Data in the process evaluation related to the therapists’ and patients’ opinions and experiences toward the feasibility of the intervention and perceived benefits will be analyzed by means of descriptive statistics. Free comments and clarifying examples may be quoted and used to describe personal experiences of the therapists or participants.

**Table 2 table2:** Measures for the process evaluation. A checkmark indicates with which measure the question is examined.

Questions	Measures			
	Therapist Log	Audio recordings	Therapist questionnaire	Patient questionnaire
To what extent did the therapists deliver the interventions as intended (fidelity)?	✓	✓	✓	

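### Table 1 and the Methods text give different names for the quality-of-life questionnaire and do not agree clearly on its post-baseline visit

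*Protocol article*

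**What the plan says.** The article names the quality-of-life questionnaire in four places.

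- **Abstract, Methods:** "Self-reported measures are the Movement Specific Reinvestment Scale, verbal protocol, Stroke and Aphasia Quality of Life Scale, and the Global Perceived Effect scale".
- **Table 1, General outcome measures:** the row reads "Stroke Specific Quality of Life Scale", followed by "T0, T2 Participation level". No T1 assessment is listed.
- **Self-Reported Measures, Stroke and Aphasia Quality of Life Scale:** the SAQOL-39 "is assessed at baseline and after the intervention to measure the health-related quality of life". The same paragraph describes it: "The questionnaire contains 39 items and is developed for people after stroke and is feasible to use for people with aphasia".
- **Abbreviations:** only the SAQOL-39-NL is listed, expanded as the Stroke and Aphasia scale.

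The abstract and Study Design define T1 as the assessment straight after the training period and T2 as the one a month later. Data Analyses plans to "compare the 2 groups (implicit and explicit) at 3 different time points (before, after, and after 1-month follow-up").

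**The concern.** Two things about this outcome should be unambiguous: which questionnaire is given, and when. On each, the schedule table and the descriptive text diverge.

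The name in Table 1 occurs nowhere else in the article, and Table 1 does not mention the SAQOL-39. Someone reading only the table would conclude that a different scale is in use. The article states feasibility in aphasia for the SAQOL-39 and makes no such statement for the scale named in the table.

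The visit decides what the result means. A T1 value describes the effect at the end of the 3-week programme. A T2 value describes what remains a month later. The Discussion treats durability at one month as a hypothesis of its own, so the two are not interchangeable. Quality of life is also the only outcome that Table 1 classes at participation level.

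**Working it through.** No arithmetic bears on this point. The check sets the statements side by side.

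**Instrument**

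| Place | Name given |
|---|---|
| Abstract, Methods | Stroke and Aphasia scale |
| Table 1 | Stroke Specific scale |
| Self-Reported Measures | Stroke and Aphasia scale, SAQOL-39, 39 items, with a reference |
| Abbreviations | SAQOL-39-NL |

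Three places agree and Table 1 stands alone. No sentence says that the two names mean the same questionnaire. The text gives no description, reference or abbreviation for a Stroke Specific scale.

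**Visit**

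| Place | Post-baseline visit for quality of life |
|---|---|
| Table 1 | T2 |
| Self-Reported Measures | after the intervention, no visit label |

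The unlabelled phrase has to be interpreted from the rest of the article:

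1. The abstract and Study Design tie T1 to the end of the intervention and describe T2 by its one-month interval.
2. Data Analyses names the three visits before, after, and after 1-month follow-up. A plain 'after' is therefore T1 in the article's own shorthand.
3. On this usage the text points to T1, a visit at which Table 1 schedules no quality-of-life assessment.
4. T2 is nevertheless also later than the intervention, and the subsection does not say that the assessment is immediate.

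**Neighbouring rows.** The verbal protocol is placed after the 3-week intervention in its own subsection and at T2 in Table 1. The Global Perceived Effect question asks about the last three weeks, yet it is listed at T2, a month after training ended. Either the article uses 'after' loosely, or this block of the table was not matched to the text. The document does not show which.

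**General sentence.** The Measurements section says that all measures are taken at T0, T1 and T2 and refers to Table 1. It cannot settle the visit, because Table 1 gives several measures fewer than three visits.

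**Number of values.** On either reading (T0 and T1, or T0 and T2), each participant has one baseline and one post-baseline score.

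**The case against.** The strongest reply is that the instrument is identifiable. The SAQOL-39 has its own subsection with a reference, an item count and a rationale, and the abstract and abbreviations agree with it. The competing name is a single table label. Nothing suggests that two questionnaires are in use, so a labelling slip is the likeliest explanation. That stands, and it limits the harm. The label still needs correcting.

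On timing, the reply is that Table 1 supplies the specific visit, and a loose 'after' is compatible with T2, as the verbal protocol row suggests. This stands in part: the visit problem is an ambiguity leaning towards conflict, not a flat contradiction. Data Analyses' naming of the visits still points the reader to T1.

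A reader might infer more than this, and the article does not support it:

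- **That assessors give the wrong questionnaire, up to all 80 planned participants (2 × 40).** Table 1 is an overview in a journal article. Nothing says that fieldwork follows it.
- **That missing or unreliable answers would concentrate in people with communication problems.** The article gives no completion data for either scale, and entry requires communicating in Dutch and following a 3-stage command.
- **That the planned analysis cannot be carried out because quality of life lacks a third visit.** Data Analyses describes a general comparison at three time points and does not say that every outcome must enter it. Table 1 openly lists some outcomes at a single visit.

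**Conclusion.** The point holds in a limited form. The instrument name in Table 1 conflicts with the abstract, the Methods text and the abbreviations. The post-baseline visit in Table 1 (T2) does not match the most natural reading of the Methods text (T1), although that text does not rule T2 out.

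The size is one secondary, self-reported outcome, with no numerical effect that can be derived from the article. Walking speed, the sample size built on it and the randomization are unaffected. The practical consequence is that a reader cannot tell whether a reported quality-of-life difference is an immediate or a 1-month effect.

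The conclusion on the visit rests on reading 'after' as Data Analyses uses it. The conclusion on the name needs no assumption. That the name is only a slip is probable but not stated. The article gives no basis for choosing between T1 and T2, so the sponsor has to settle it.

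**What to change.** 1. In Table 1, change the quality-of-life row to SAQOL-39 (SAQOL-39-NL, as in the abbreviations).
2. Have the sponsor confirm from the forms in use whether the post-baseline assessment is at T1 or T2. State that same visit label in Table 1 and in the Stroke and Aphasia Quality of Life Scale subsection.
3. Because there is one post-baseline value, state that the arms are compared at the confirmed visit with the T0 score as covariate. This uses data already collected and leaves the three-visit analysis to outcomes measured three times.
4. If the forms show that another questionnaire was used at any visit, report those scores separately and do not pool them with SAQOL-39 scores.

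The cost is one table row, one sentence on the visit, one sentence on the analysis and a look at the forms. No visit or participant burden is added. The only possible loss is that scores from a different questionnaire, if any exist, could not contribute to the SAQOL-39 comparison.

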#### Dynamic Gait Index

The DGI is a physical performance test that assesses the gait, balance, and fall risk and has shown to have a good reliability and validity in people after stroke [44,45]. Eight different tasks related to the balance and gait, for example, walking, turning, and stepping over objects are assessed [46]. The performance will be scored according to the modified DGI as proposed by Shumway and Cook as the extended scoring system has shown to possess good psychometric properties [42,47].

#### Dual Task

In this study, people will be asked to complete a tone-counting task similar to that proposed by Wilson et al [48]. In this task, people will be exposed to 4 different sounds (buzzer, ping, tone and bell ring) in a randomized order over a 30-s time period. They will be asked to only count a specific target sound (eg, bell ring) and ignore the other 3 distracting sounds. The task will be performed twice, once as a single task and once while walking concurrently (dual task). The actual number of tones will be compared with the estimate number of tones by the participants. Error scores (actual minus estimate) will be calculated as a measure for the dual-task performance.

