### Sample Size

The sample size calculation is based on a randomized controlled trial with equal group sizes and “walking speed” (10-meter walking test, 10MWT) as a primary outcome measure [30]. The power is set at beta=.80, the significance level at alpha=.05, and a standard deviation of 0.23 m/s [31]. To demonstrate a significant change in walking speed, the minimal clinically important difference (MCID) is used and set at a minimum change of 0.16 m/s [32,33]. The calculations resulted in a minimum group size of 33 participants per group. Taking into account that 20% (7/33) of participants may be lost during (dropout) and after the intervention (loss to follow-up), this study aims to recruit 40 participants per group.

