### Implicit Motor Learning

Scientific evidence describes that implicit learning is typically characterized by robust dual-task performance, durable performance over time, and less accumulation of explicit rules [24,56]. The dual-task measure and the 1-month follow-up session were specifically chosen with respect to these implicit characteristics. First, walking while concurrently carrying out a secondary (tone counting) task [48] places high information-processing demands on the learners. In contrast to explicit learners, implicit learners showed that performance was not disrupted in dual-task conditions, which indicates that they may be able to free up attentional resources to perform the secondary task [24]. We therefore predict that the implicit condition will remain stable under secondary task burden. For this reason, implicit learning may be particularly beneficial for those who experience cognitive impairments that are commonly seen in people after stroke.

Then, a recent study by Tse et al [25] found performance improvements after a 2-day separation; however, they recommended to include a longer separation to test skill consolidation. This study will therefore evaluate performance after the 1-month follow-up period. It is hypothesized that performance improvements in the implicit group will remain robust over a longer period (1-month follow-up). To make statements about long-term effects within rehabilitation, it may be desirable for future studies to include even longer follow-up periods (>3 months). Finally, a verbal protocol will be assessed because it is hypothesized that participants within the implicit learning group will report fewer explicit rules than the control group, which would be in line with the findings of earlier studies [23,24]. Even though the starting point of the explicit intervention is to use many verbal explicit instructions and provide more details on the motor performance, the exact number of explicit rules will be tailored to the ability of the patient to process these rules. Therefore, in practice, some patients might receive higher numbers of explicit rules than others. Still, we hypothesize that the explicit group will require more explicit rules compared with the implicit group.

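### Dual-task performance is scored as a signed counting error, and no gait result is defined for a trial presented as a walking assessment (secondary outcome)

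*Protocol article*

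**What the plan says.** In the Dual Task section, participants hear four sounds over 30 seconds, count one target sound and ignore the other three. They do this once alone and once while walking. The comparison is of counts: "The actual number of tones will be compared with the estimate number of tones by the participants". The scoring rule is then fixed: "Error scores (actual minus estimate) will be calculated as a measure for the dual-task performance". No absolute value, square or percentage is taken. No speed, distance or step measure is named for the walking trial.

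Elsewhere the same trial is presented as an assessment of walking. The abstract says "Walking performance will be assessed with the 10-meter walking test, Dynamic Gait Index, and while performing a secondary task (dual task"). Walking Performance Measures gives the purpose as testing the robustness of performance: "walking will also be assessed over a longer period (1-month follow-up) and under secondary task loading". Table 1 lists the dual task under walking performance at T0, T1 and T2. In the Discussion, under Implicit Motor Learning, the authors say the measure was chosen for its link to implicit learning, and write: "We therefore predict that the implicit condition will remain stable under secondary task burden".

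Data Analyses compares the two groups at the three time points by a repeated measures analysis.

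**The concern.** There are two separate problems.

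**The score.** With one target among three distractors, a participant can miss targets (positive score) or count distractors (negative score). The best result is zero, in the middle of the scale, so a group mean near zero can come from accurate counting or from large errors in both directions. A repeated measures comparison of such scores tests whether the arms differ in direction of miscounting. The prediction is about how well performance holds up.

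**The construct.** The trial is meant to show whether walking holds up under load, but its only defined result is a tone count. People doing two tasks at once can protect one at the expense of the other. If gait gives way and counting is preserved, the defined score shows no cost.

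At stake is the evidence for one of the three features of implicit learning that the Discussion sets out to examine (robustness under a second task, durability over time, fewer explicit rules).

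**Working it through.** **The plan's own figure.** The article gives no number for the dual-task outcome. Its only sample-size figure is for walking speed: "The power is set at beta=.80, the significance level at alpha=.05, and a standard deviation of 0.23 m/s", with a difference of 0.16 m/s. Taking .80 as the power and a two-sided test,

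n = 2 × (1.960 + 0.842)² × 0.23² / 0.16² = 2 × 7.85 × 2.066 = 32.4, so 33 per group.

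This agrees with the article. It is used below only as a realistic arm size.

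**What the signed score does.** Score = actual − estimate.

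- One participant misses 3 targets (+3) and another over-counts by 3 (−3): mean (3 − 3)/2 = 0, the same as two perfect counters.
- Both then become perfect: the changes are −3 and +3, mean change 0, although both improved.

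**Effect on power.** The article gives no error SD or bias, so both are assumed. Errors are normal, rounded to whole tones, 33 per arm, compared by a two-sample t test at two-sided .05. Rejection rates are from simulation, and repeated runs agree to within about two percentage points.

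| Assumed bias, arm A v B | Assumed SD, A v B | Mean absolute error, A v B | Signed score rejects | Absolute score rejects |
|---|---|---|---|---|
| 0 v 0 | 1 v 2 | 0.76 v 1.58 | 5% | 91% |
| 0 v 0.5 | 1 v 2 | 0.76 v 1.62 | 24% | 94% |
| 0 v 1 | 1 v 1.5 | – | 86% | 84% |
| 0 v 1 | 1 v 1 | 0.76 v 1.15 | 97% | 49% |

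**Hand check by normal approximation.** Rounding to whole numbers adds 1/12 = 0.083 to each variance.

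- Signed, row 2: SE = √[(1.083 + 4.083)/33] = 0.396; 0.5/0.396 = 1.26; Φ(1.26 − 1.96) = 0.24.
- Signed, row 4: SE = √[(1.083 + 1.083)/33] = 0.256; 1/0.256 = 3.90; Φ(3.90 − 1.96) = 0.97.
- Absolute, row 1: variances 1.083 − 0.76² = 0.505 and 4.083 − 1.58² = 1.587; SE = √(2.092/33) = 0.252; (1.58 − 0.76)/0.252 = 3.26; Φ(3.26 − 1.96) = 0.90.
- Absolute, row 4: variances 0.505 and 2.083 − 1.15² = 0.761; SE = √(1.266/33) = 0.196; (1.15 − 0.76)/0.196 = 1.99; Φ(1.99 − 1.96) = 0.51.

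Row 1 for the signed score needs no calculation. Both means are zero, so it rejects at the alpha level.

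**Stated construct against defined measure.** The abstract, Walking Performance Measures and Table 1 all place the trial under walking performance. The Dual Task section defines a tone count only. The 10-meter walking test is described under Measurements and in its own section, and neither says that it is done with the second task. The rationale in the Discussion has two parts: earlier work in which "implicit learners showed that performance was not disrupted in dual-task conditions", and the idea that attention is freed for the second task. The counting score addresses the second part. Nothing defined addresses whether gait is disrupted.

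**The case against.** - **This is a secondary outcome.** The Research Question concerns walking speed, which is the primary outcome and the only basis of the sample size. The dual task tests one of three features of implicit learning. This stands and limits the weight of the point.
- **Absolute error is not always better.** If participants mainly miss targets and the arms differ in how many, the signed score can be the more powerful, as the last row of the table shows. This stands. A reader might infer from the first row alone that signed scoring removes the power of the comparison. The article gives no error distribution, so that row is one end of a range.
- **The repair is partial.** A participant who misses two targets and counts two distractors reports the right total. Taking the absolute value does not reveal that. This also stands.
- **An article condenses.** It does not say outright that signed values will be averaged, and the full protocol may take the magnitude. But the article does not leave the score open: it prints a formula with a sign, and the stated analysis compares groups over time. A reader following the text would compute the signed score.
- **The gait half argues from silence.** The article calls the error one measure of dual-task performance and does not say that no gait reading is taken. A reader might infer that none exists, or that a participant could stop walking and be scored as robust. The text supports neither. It does support a narrower statement: walking under load is promised in three places, and no result is defined that would show it.

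**Conclusion.** The point holds as a limited one about a secondary outcome. The printed formula measures direction of miscounting, not accuracy, and it is the only result defined for a trial described as a walking assessment. A null result on it would not show that dual-task performance was stable, and gait sacrificed to protect counting would go unseen.

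The size in terms of power cannot be fixed from the article. Under the assumptions stated, the comparison of signed with absolute error runs from 5% v 91% (symmetric errors, different spread) to 97% v 49% (same spread, bias in one arm only). The case for absolute error therefore rests mainly on meaning: it falls when counting improves, whichever way the participant errs.

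A reader might conclude that this undermines the trial's central claim. The documents do not support that. The research question, primary outcome and sample size do not depend on the dual-task score, and the prediction is partly about attention for the second task, which counting does address.

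**What to change.** 1. **Scoring.** Make absolute error, |actual − estimate|, or the same as a percentage of targets presented, the dual-task accuracy score. Compare it between arms with the single-task absolute error taken into account. Keep signed error as a description of direction. This uses counts already recorded. The price is some loss of power if errors run mainly one way. Misses and false counts within one trial will still cancel, and the report should say so.
2. **Gait under load.** Record walking speed in the dual-task trial, from distance covered or time taken, and report it beside the counting score, adjusted for T0. This needs one extra reading during a walk that is already performed. If such a reading is already taken, name it in the Dual Task section.
3. **Participants already tested.** The Results section has enrolment running from March 2017 to an expected July 2018, so some dual-task walks may have no gait reading. Report how many. Where the reading is missing, limit the robustness claim to counting performance.

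The scoring rule should be settled before the dual-task data are compared by arm.
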